## VI - 2 - SECONDARY ENDPOINTS

The secondary endpoints will be as follows:

- Area under the curve of pain over the past 48 hours, assessed every fortnight using a numeric scale from 0 to 100 at 1 year;
- Functional assessment at 1 year (Quebec scale);
- Quality of Life assessment at 1 year (MOS SF-12 questionnaire);
- TWIST at 1 year (pain);
- Number of days of sick leave between 6 months and 1 year after enrolment. We have not taken into account the total number of days of sick leave as, by definition, the intervention requires the patients to be available for the duration of the treatment, which will involve sick leave.

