## VII - 3 - FOLLOW-UP VISITS after the intervention

Patients will undergo follow-up at Months 3, 6 and 12. Follow-up will be done by post or email, depending on the patient’s preference, together with a telephone call if no response is received.

The following data will be evaluated:

- Professional status and return to work;
- Periods of sick leave since the previous visit (dates and number of days of sick leave);
- Assessment of pain over the past 48 hours, assessed using a numeric scale from 0 to 100;
- Lower back pain progress;
- Treatment since the previous visit;
- Adverse events collected;
- Functional indices: Quebec scale;
- Anxiety/Depression: HAD questionnaire;
- Quality of Life: MOS SF-12 questionnaire;
- Fear-avoidance beliefs: FABQ questionnaire (only at the Month 12 assessment);
- Coping strategies: CSQ questionnaire (only at the Month 12 assessment);
- Treatment satisfaction (only at the Month 12 assessment).

Pain over the past 48 hours will also be systematically evaluated once every fortnight by phone (using a numeric scale from 0 to 100). VOICE RESPONSE SYSTEM

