## IX -1- 6- Secondary analyses

A linear mixed effects regression model will be used to compare the variations between the groups of the quantitative secondary endpoints (number of days of sick leave, number of periods of sick leave, pain, Quebec scale, MOS SF-12, HAD, FABQ and CSQ). The variable to be studied will therefore be the difference between the randomisation value (D0) and that of interest (1 year), as well as the difference between the randomisation visit and those of the interim visits (3 months and 6 months). The difference in the Δ between the groups will be modelled with the following fixed effects: the group variable (2 modalities), the enrolment value as a quantitative covariate (centred variable), the visit variable (3 modalities) and the interaction between the time and the visit, allowing us to estimate the treatment effect at each visit. The model will therefore allow us to compare the adjusted means (to the baseline value and the values of the interim visits) of the variations between the final visit and the enrolment visit (as well as between the interim visits and the enrolment visit). A random effect on the patient will be added to this model in order to take into account the correlation induced by the repetition of the measurements performed in the same patient. This linear mixed model for repeated measurements (MMRM) allows the assessments performed at each visit to be taken into account, as well as the randomly missing data (the model will also integrate the endpoint values at the different visits, enrolment variables which are potentially predictive of the missing data). The area under the curve of pain between enrolment and 1 year, assessed every week, will be calculated using the trapezoidal rule and compared using the non-parametric Mann–Whitney U test. The Q-TWIST will be calculated from the percentage of time spent by a patient in various states (percentage of time spent in inactivity, time spent with acceptable pain (less than 3 on a scale from 0 to 10 which corresponds to the PASS), time spent with pain greater than 3). The values assigned to these states will be defined at the time of the blind review of the data. The means will be compared using the non-parametric Mann–Whitney U test.

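### The secondary mixed model lists a time-by-visit interaction where its stated purpose needs group by visit, so as written it gives one group effect averaged over Months 3, 6 and 12

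*Protocol*

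**What the plan says.** Section IX-1-6 of the protocol specifies the model term by term. The response is the change from enrolment. The fixed effects are group (two levels), the centred enrolment value, "the visit variable (3 modalities) and the interaction between the time and the visit, allowing us to estimate the treatment effect at each visit". The next sentence says the model will compare the adjusted means "of the variations between the final visit and the enrolment visit (as well as between the interim visits and the enrolment visit"). The random part is a single patient effect: "A random effect on the patient will be added to this model".

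The outcomes assigned to this model are sick-leave days, sick-leave periods, pain, Quebec, SF-12, HAD, FABQ and CSQ. Section VII-3 gives the schedule: "Patients will undergo follow-up at Months 3, 6 and 12", with FABQ and CSQ collected at Month 12 only.

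Section VI-2 fixes the time point of the two patient-reported endpoints that clearly use this model: "Functional assessment at 1 year (Quebec scale") and "Quality of Life assessment at 1 year (MOS SF-12 questionnaire"). It also restricts sick-leave days to the second half of the year.

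The statistical paragraph of the Summary names only a linear mixed model. No section lists a group-by-visit or group-by-time term.

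**The concern.** An interaction between time and visit is an interaction of a factor with itself. It cannot carry a treatment effect, because group is not in it. Group therefore enters only as a main effect, which means one coefficient shared by all visits. The sentence promises a treatment effect at each visit, and the listed terms cannot supply one.

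Function and quality of life are defined at 1 year. A coefficient averaged over Months 3, 6 and 12 answers a different question whenever the effect changes over the year. An early benefit that has faded would still show in the average, and a benefit that builds up late would be diluted. If sick-leave days are entered visit by visit, a common group term would also bring back the early intervals. Section VI-2 leaves those out on purpose, because attending the intervention itself involves sick leave.

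**Working it through.** **The plan's own figure.** The protocol has no calculated figure for the secondary model. Its only calculation (section IV-3) is for the primary endpoint, and it reproduces: n per arm = [1.96·√(2·0.75·0.25) + 0.8416·√(0.70·0.30 + 0.80·0.20)]² / 0.10² = 293.2, so 294 per arm and 588 in total, against 600 stated. The present point does not depend on it.

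**Step 1: what the listed terms can estimate.** Hold the enrolment value fixed and take the six cells of 2 groups by 3 visits.

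| Fixed effects | Columns | Rank | Separate group contrasts |
|---|---|---|---|
| Intercept, group, visit | 4 | 4 | 1 |
| As written, time in months | 7 | 4 | 1 |
| As written, time as categories | 8 | 4 | 1 |
| Group by visit instead | 6 | 6 | 3 |

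The written interaction leaves the rank at 4 under either coding of time. The group difference at visit v is the mean in cell (1, v) minus the mean in cell (0, v). Every term except the group main effect cancels, so the difference is the same coefficient at Months 3, 6 and 12. With group by visit there are three separate contrasts, and the Month 12 effect can be estimated.

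**Step 2: what the single coefficient is.** Let d3, d6 and d12 be the true group differences at the three visits. With complete data and a patient random intercept, the coefficient estimates

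(d3 + d6 + d12)/3,

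so its gap from the 1-year effect is

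(d3 + d6 + d12)/3 − d12 = (d3 + d6 − 2·d12)/3.

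This does not depend on the SD or the correlation. When later visits are missing, the weights shift towards the earlier ones.

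**Step 3: illustrations.** The effect profiles below are assumptions. The protocol gives none.

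| Assumed benefit at M3, M6, M12 | Averaged effect | Gap from M12 |
|---|---|---|
| 5, 5, 5 | 5 | 0 |
| 9, 6, 0 | 15/3 = 5 | +5 |
| 0, 3, 6 | 9/3 = 3 | −3 |
| 0, 5, 10 | 15/3 = 5 | −5 |

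A fit to one simulated data set (300 per arm, complete, patient and residual SD both 12) agrees. With benefits 0, 5, 10 the written model gave 5.0, and group by visit gave 9.9 at Month 12.

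**Step 4: what this could do to a test.** Assume 300 per arm, complete data, SD 22 and mean between-visit correlation 0.55.

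- SE of the averaged effect = 22·√((1 + 2·0.55)/3)·√(2/300) = 22·0.837·0.0816 = 1.50.
- SE of the Month 12 contrast = 22·0.0816 = 1.80.

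Two-sided rejection rates at 5%, with the SD varied from 15 to 30 because the protocol gives none:

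| SD | Profile 9, 6, 0: averaged effect (5) significant | Profile 0, 3, 6: averaged effect (3) significant | Profile 0, 3, 6: M12 contrast (6) significant |
|---|---|---|---|
| 15 | 99.8% | 83% | 99.8% |
| 22 | 91% | 51% | 92% |
| 30 | 68% | 31% | 69% |

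In the first profile the true 1-year effect is zero. Under a constant effect the problem vanishes. These rates show the direction of the error and say nothing about what this trial's data will look like.

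**Step 5: which outcomes are affected.**

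- Affected: Quebec, SF-12, HAD and the pain score, which are measured at all three visits. Sick-leave days and periods are affected where they are entered by visit.
- Not affected: FABQ and CSQ, which have only a Month 12 follow-up value, so their group coefficient is already the 1-year effect.
- Not in this model: the primary endpoint (Chi-squared test), pain AUC and TWIST (Mann–Whitney U test).

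**The case against.** The strongest reply is that the intention is plain. The sentence itself says the interaction is there to give the treatment effect at each visit, the next sentence compares the final and interim visits separately, and only group by visit does that. A programmer following the text would meet a redundant term, find no visit-specific contrast, and see that something was wrong. Section IX-1 also provides for a separate statistical analysis plan, validated before database freeze, where the model would be written out again. All of this stands, and it lowers the severity.

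It does not make the text right. The protocol does not leave the model open: it lists the terms and gets one wrong, and nothing elsewhere in it supplies the missing one. A later plan would have to copy a redundant term or depart from the protocol.

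A reader might infer more than the documents support:

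- *That a pooled 3-to-12-month effect was chosen as the target.* The stated purpose says the opposite.
- *That the trial will report an averaged effect as its 1-year result.* An analyst would have to ignore the promised visit-specific output and then mislabel the pooled coefficient.
- *That all secondary results, or the main conclusion, are at risk.* The list of affected outcomes in the working shows otherwise.
- *That the size of the error is known.* No SD, correlation or effect profile for these outcomes is given.

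**Conclusion.** The point holds as an error in an operative analysis rule. As written, the model has one group coefficient common to all visits, so it can give neither the per-visit effects that section IX-1-6 promises nor a 1-year effect for the function and quality-of-life endpoints of section VI-2. That follows from the listed terms and needs no numerical assumption beyond reading time and visit as the same factor, which the schedule supports.

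The severity is moderate to minor. It is most likely a drafting or translation slip that would probably surface in programming. The error matters only if the text is coded literally and the Month 12 effect differs from the average of the earlier two. Its size, (d3 + d6 − 2·d12)/3 with complete data, cannot be fixed from the protocol.

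**What to change.** In section IX-1-6, change the interaction term so that it is between the group and the visit, by replacing the word 'time' with 'group'. Add one sentence: the Month 12 group contrast from that interaction is the estimate for the 1-year secondary endpoints analysed with this model. Carry the same wording into the statistical analysis plan.

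FABQ and CSQ need no change. The cost is one line of text before unblinding. Sample size, data collection, trial conduct and the primary analysis are unchanged.

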## IV - 3 - REQUIRED NUMBER OF SUBJECTS

The return-to-work rate at 1 year is estimated to be 70% in the control group. The hypothesis is to reach 80% in the intervention group. With a 5% risk and a power of 80%, a total of 600 patients are planned to be enrolled: 300 patients in the short spa therapy group and 300 patients in the control group. Taking into account the risk of loss-to-follow-up, 700 patients will be enrolled.

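### The secondary-endpoint model labelled MMRM names only a patient random effect; taken literally it averages the variance over visits and can miscalibrate the 1-year tests

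*Protocol*

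**What the plan says.** Protocol section IX-1-6 puts eight endpoints into one linear mixed model: "number of days of sick leave, number of periods of sick leave, pain, Quebec scale, MOS SF-12, HAD, FABQ and CSQ". The response is the change from D0. The fixed effects are group, centred baseline value, and "the visit variable (3 modalities) and the interaction between the time and the visit, allowing us to estimate the treatment effect at each visit". I read that interaction as group by visit, since only this gives a treatment effect at each visit.

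One term deals with the dependence within a patient: "A random effect on the patient will be added to this model in order to take into account the correlation induced by the repetition". The next sentence names the whole: "This linear mixed model for repeated measurements (MMRM) allows the assessments performed at each visit to be taken into account". No residual covariance structure, robust variance or degrees-of-freedom method is given.

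Three other places bear on the point:

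- Section VI-2 asks for the Quebec scale and SF-12 at 1 year, and for sick-leave days between 6 months and 1 year.
- Section VII-3 collects sick leave for the time since the preceding contact, and contacts are at Months 3, 6 and 12. The FABQ entry there reads "Fear-avoidance beliefs: FABQ questionnaire (only at the Month 12 assessment"; the CSQ entry carries the same restriction.
- Section IX-1 says that a statistical analysis plan will be written and validated before database freeze. It is not shown.

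**The concern.** The section does more than leave the covariance open. It names one term and gives it the task of carrying the correlation between repeated measurements. A random patient intercept with default (independent, constant-variance) residuals implies one variance for all three visits and one correlation for every pair of visits. That is compound symmetry. The label MMRM ordinarily stands for an unstructured covariance by visit, so the label and the stated term pull apart.

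What matters is the Month 12 comparison. Under compound symmetry its standard error is built on the average of the three visit variances, not on the Month 12 variance. If Month 12 is the most variable visit, the confidence interval is too narrow and the 5% test rejects too often. If it is the least variable visit, the interval is too wide and power is lost.

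The protocol itself gives a reason to expect unequal variances for one modelled endpoint. Sick-leave days counted between contacts cover about 3 months at Month 3, 3 months at Month 6 and 6 months at Month 12.

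**Working it through.** **The plan's own figure.** The protocol gives no SD, correlation or power for this model. Its only sample-size figure is for the primary endpoint (section IV-3), which assumes return to work of 70% under control and 80% under spa therapy: "With a 5% risk and a power of 80%, a total of 600 patients are planned to be enrolled". With pooled variance and a two-sided 5% test, the number per arm is

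[1.960·√(2·0.75·0.25) + 0.842·√(0.70·0.30 + 0.80·0.20)]² / 0.10² = (1.200 + 0.512)² / 0.01 ≈ 293.2, hence 294.

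That is 588 in total, within 3% of 600; power at 300 per arm is 80.9%. The figure reproduces and sets the scale: about 600 evaluable of 700 enrolled, an implied loss of 100/700 = 14.3%.

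**Formula for the model in dispute.** With complete data and a group-by-visit model, the Month 12 estimate is the difference in means at Month 12, with true variance 2·s₁₂²/n. Compound symmetry replaces s₁₂² by the mean of the three visit variances. So

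- ratio r = model-based SE / true SE = √[(s₃² + s₆² + s₁₂²)/3] / s₁₂
- actual two-sided type I error = 2·[1 − Φ(1.96·r)]

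**Inputs.** All SDs and correlations below are assumptions. Correlations are 0.70 (M3–M6), 0.45 (M3–M12) and 0.60 (M6–M12). The dropout column uses 350 per arm, with data missing completely at random and retention of 93% at Month 6 and 600/700 at Month 12. It takes the best-fitting compound-symmetry parameters and compares the model-based SE with the true (sandwich) SE.

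| SDs at M3/M6/M12 | r, complete | Type I error, complete | Type I error, dropout |
|---|---|---|---|
| 1.0/1.0/1.0 | 1.00 | 5.0% | 5.2% |
| 0.9/1.0/1.1 | 0.91 | 7.4% | 7.8% |
| 0.8/1.0/1.2 | 0.84 | 9.8% | 10.5% |
| 1.1/1.0/0.9 | 1.11 | 2.9% | 3.0% |
| 1.2/1.0/0.8 | 1.27 | 1.3% | 1.4% |

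One line in full, for 0.9/1.0/1.1: √[(0.81 + 1.00 + 1.21)/3] = 1.003; r = 1.003/1.1 = 0.912; 2·[1 − Φ(1.788)] = 7.4%.

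The first row isolates the unequal correlations. They move the SE by 0% with complete data and about 1% with dropout. With an unstructured covariance, r is 1.00 in every row.

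**A route to rising variance.** Suppose an outcome SD of 25 at each visit and a correlation with baseline of 0.70, 0.60 and 0.45. The residual SDs are 25·√(1 − ρ²) = 17.85, 20.0 and 22.33. The pooled SD is √[(17.85² + 20.0² + 22.33²)/3] = 20.1; 22.33/20.1 = 1.11; the type I error is about 7.7%.

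**Sick-leave days.** Set the Month 3 and Month 6 SDs to 1. If variability per unit of time is constant, doubling the window multiplies the SD by √2 = 1.41 when its two halves are uncorrelated, and by 2 when they are perfectly correlated.

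- SD 1.41: r = √[(1 + 1 + 2)/3]/1.414 = 0.816; 2·[1 − Φ(1.600)] ≈ 11%.
- SD 2: r = √[(1 + 1 + 4)/3]/2 = 0.707; 2·[1 − Φ(1.386)] ≈ 17%.

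**FABQ and CSQ.** With one follow-up value per patient, the variance of a patient random effect cannot be separated from residual error, so the stated model cannot be fitted to them as written.

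**The case against.** The strongest reply is that covariance type, estimation method and degrees of freedom are usual matters for the analysis plan, which is promised and not shown. The protocol never says that residuals are independent or of equal variance, and a patient random effect can be combined with a heterogeneous or correlated residual matrix.

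Part of this stands. A reader might infer that the protocol forces equal variances and correlations and so yields a wrong standard error at 1 year. The text does not support that: the residual structure is unstated, and without any SDs a wrong standard error cannot be demonstrated. The direction is also open. Falling variance gives a conservative test, and equal variance a correct one. Nor does the uneven spacing of visits, through unequal correlations, add anything material.

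The scope is limited too. Of the five endpoints in section VI-2, the pain area under the curve and TWIST go to the Mann–Whitney test. Quebec, SF-12 and sick-leave days remain. HAD, the visit pain score and the number of sick-leave periods are modelled but not listed there. Section IX-1-5 tests the primary endpoint by Chi-squared.

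What does not stand is that this is only missing detail. The protocol names a covariance term and its purpose. An analysis plan that follows it literally takes over the problem, and one that uses an unstructured covariance departs from the stated term.

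**Conclusion.** The point holds in conditional form. As written, the only stated device for repeated measures is a patient random effect. Read as a random intercept with default residuals, it makes the Month 12 standard error rest on a variance averaged over three visits.

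Under the assumed SDs, that standard error is about 9% to 17% too small if variance rises moderately and about 11% to 27% too large if it falls. Sick-leave days have the best support in the document, because of the longer last window. Their 11% to 17% still assumes that variability per unit of time is constant and that days are counted from one contact to the next.

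This affects secondary endpoints with repeated follow-up values, and no conclusion about return to work depends on it. It is worth correcting because a better specification is available at almost no cost.

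**What to change.** For endpoints measured at Months 3, 6 and 12 (Quebec, SF-12, HAD, visit pain score, sick-leave days and periods), replace the patient random effect in section IX-1-6 with an unstructured 3×3 within-patient covariance by visit, fitted by REML with Kenward-Roger degrees of freedom. A baseline-by-visit term is a reasonable option, though no calculation here shows harm from a common baseline slope.

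For FABQ and CSQ, use a baseline-adjusted linear model (ANCOVA) at Month 12, without a patient random effect.

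Carry the same wording into the analysis plan before unblinding, so that the two documents agree. The unstructured matrix has six parameters (three variances, three covariances) against two for compound symmetry. Four more are negligible with about 600 patients. No data collection, sample size or primary analysis changes.

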# VII – PATIENT STUDY PLAN

## VII - 1 – D0 - ENROLMENT VISIT

Patients who may be eligible for enrolment will be referred to the Department of Physical Medicine and Rehabilitation at Cochin, Clermont-Ferrand, Montpellier or Nancy, or else to an independent assessor in Aix les Bains or Dax, in order to be enrolled in the study.

The investigator will systematically confirm the inclusion and exclusion criteria at the enrolment visit. First of all, the investigator will clearly explain to the patient the implications of participating in a cohort study with follow-up by post or email at Months 3, 6 and 12 and a pain assessment by phone every fortnight for 1 year. The patients will also be systematically informed that, for scientific reasons, they will not be given details of any of the research hypotheses until the end of the study. At the end of the study, the patients in the control group will not be able to benefit from the study results. After 1 year of follow-up, patients in the control group who are still on sick leave will no longer justify this type of intervention. If the patient agrees to participate in the cohort study, he or she will sign the initial informed consent form (ICF1).

After signing ICF1, the patients will be randomised using secure computerised randomisation software. The patients randomised into the short spa therapy programme will be offered the treatment and, if they accept, they will sign the second informed consent form (ICF2). For these patients, an enrolment form will be sent by fax to the spa therapy centre of reference, to the Clinical Research Unit (URC) and to the French Association for Spa Therapy Research (AFRETH) to plan the organisation of this treatment.

The following information will be collected in the case report form:

- - Patient contact details (surname, first name, address, email, telephone number(s));
  - Demographic parameters (age, sex);
  - Socioprofessional parameters (level of studies, profession and start date of sick leave);
  - Clinical parameters regarding the lower back pain (date of diagnosis of lower back pain, date of onset of current episode and main aetiology);
  - Assessment of pain over the past 48 hours, assessed using a numeric scale from 0 to 100;
  - Previous and ongoing treatment for lower back pain;
  - Functional indices: Quebec scale;
  - Anxiety/Depression: HAD questionnaire;
  - Quality of Life: MOS SF-12 questionnaire;
  - Fear-avoidance beliefs: FABQ questionnaire;

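### Section IX-1-6 calls fortnightly pain data weekly, and its Q-TWIST states do not divide follow-up time into exclusive and complete parts

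*Protocol*

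**What the plan says.** **AUC of pain.** Protocol VI-2 lists the endpoint as "Area under the curve of pain over the past 48 hours, assessed every fortnight using a numeric scale from 0 to 100". VII-3 sets the collection: "Pain over the past 48 hours will also be systematically evaluated once every fortnight by phone". The Summary, the General Outline and VII-1 also give a fortnightly interval. The analysis section, IX-1-6, says instead: "The area under the curve of pain between enrolment and 1 year, assessed every week, will be calculated using the trapezoidal rule". The comparison is a Mann-Whitney test with no covariate. Enrolment pain is recorded on the same recall period and scale (VII-1: "Assessment of pain over the past 48 hours, assessed using a numeric scale from 0 to 100").

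**TWIST.** VI-2 lists a TWIST for pain at 1 year. IX-1-6 computes a Q-TWIST from the percentage of time in three states. The first is inactivity, with no definition. The other two are "acceptable pain (less than 3 on a scale from 0 to 10 which corresponds to the PASS), time spent with pain greater than 3". On the weights, it says "The values assigned to these states will be defined at the time of the blind review of the data". It then says that the means are compared with a Mann-Whitney test.

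**Other quantitative endpoints.** IX-1-6 puts these, including pain at the 3, 6 and 12 month visits, into a mixed model with the enrolment value as a covariate.

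**The concern.** The protocol contradicts itself on the interval between the pain scores that make up the AUC. A programmer who takes the analysis section at its word could use the wrong spacing.

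The Q-TWIST problem goes deeper. An index built from shares of time needs states that do not overlap and that together cover all the time. The states in IX-1-6 do neither, so two analysts could follow the text faithfully and get different values for the same patient. The stated quantity (means) and the stated test (ranks) also do not match, which leaves open what a result would say.

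The AUC comparison also passes over a baseline measurement that the trial already collects and already uses for its other quantitative endpoints.

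**Working it through.** **1. The plan's own figure.** The protocol gives no sample size or power for the AUC or the Q-TWIST. Its one calculation (IV-3: 70% against 80%, 80% power, 5%, two-sided by IX-1-5) reproduces:

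n per arm = [1.960·√(2·0.75·0.25) + 0.842·√(0.7·0.3 + 0.8·0.2)]² / 0.10² ≈ 294

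That is 588 in total, against 600 planned. Nothing below touches it.

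**2. Interval.** Five places in the protocol say fortnightly and one says weekly. To see what this does to the AUC, assume for illustration only that pain falls as 30 + 30·exp(−t/13), with t in weeks from 0 to 52.

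| Calculation | AUC |
|---|---|
| Exact | 1942.9 |
| Trapezoids, weekly, 53 points | 1943.0 |
| Trapezoids, fortnightly, 27 points | 1943.6 |
| Fortnightly points treated as one week apart | 971.8 |

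The trapezoidal rule works on fortnightly data. Only a wrong spacing does harm: it halves every AUC. If applied to all patients alike, that would leave the ranks as they are but misstate the values.

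**3. Boundary score.** The pain states cover scores below 3 and above 3, so exactly 3 has no state. How often this would occur depends on assumed distributions:
- Whole-number 0 to 10 scores, roughly normal, mean 2 to 5, SD 2 to 2.5: P(2.5 < X < 3.5) = 12% to 20% of assessments.
- Whole-number 0 to 100 scores, mean 20 to 50, SD 22, no rounding habit: P(29.5 < X < 30.5) = 1.2% to 1.8%.
- If patients answer 0 to 100 in tens, the share moves towards the first range.

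**4. Scale.** The cut-off of 3 is on 0 to 10; the data are on 0 to 100. Rescaling by ten is simple, but the text does not do it. A literal 3 applied to the collected scores would put almost all of them in the worse state.

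**5. Overlap.** Every time point has a pain level. If pain states cover all the time (boundary aside) and a share a is also counted as inactivity, the shares sum to 1 + a. For a = 0.2 to 0.5 (assumption) that is 1.2 to 1.5, or 120% to 150%.

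**6. Test and quantity.** The Mann-Whitney test compares two distributions through ranks. It is not a test of a difference in means, and a mean difference needs its own estimate and interval.

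**7. Enrolment pain.** In a linear analysis, adjustment leaves a fraction 1 − r² of the variance, where r is the correlation of enrolment pain with AUC. The protocol gives no r; assume 0.3 to 0.5.
- r = 0.3: 1 − 0.09 = 0.91, so 9% is removed; 1/0.91 = 1.10, equal to about 10% more patients.
- r = 0.5: 1 − 0.25 = 0.75, so 25% is removed; 1/0.75 = 1.33, equal to about 33% more patients.

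**The case against.** The best defence is that these are wording slips in two secondary endpoints and that a SAP, promised in IX-1 before database freeze and unblinding, can settle them. That is fair for the interval, which is a one-word correction, and for the rescaling. It does not cover the Q-TWIST states: there the protocol states a rule, and the rule as stated does not partition time. That is more than missing detail.

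Several stronger readings are tempting, and the documents do not support them.

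- *The AUC cannot be computed as planned.* It can. The trapezoidal rule gives practically the same value at either spacing, and the curve has its starting value at enrolment.
- *Missed calls shrink the AUC and favour the arm with more losses.* IX-1-6 defines the AUC from enrolment to 1 year, so a curve cut short is not the stated endpoint. The handling rule matters: in the illustration, a last call at week 26 gives 1117.9 if truncated and 2003.4 if carried forward. But such a rule is commonly left to the SAP. The size of any bias would also need loss rates by arm. The protocol gives none; 700 enrolled for 600 implies only 1 − 600/700 = 14.3% overall.
- *The weights can be tuned to the result.* They are set at a blind review, and IX-1 provides for a blinded statistician, so the plan gives no knowledge of arm when they are chosen.
- *Ignoring enrolment pain makes the AUC test invalid.* It does not. An unadjusted rank test in a randomised comparison is valid; what is lost is precision. Pain at the three visits is adjusted in the mixed model.

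**Conclusion.** The point holds as a set of correctable defects in IX-1-6. Four follow from the text alone:

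- the weekly interval contradicts the fortnightly one given everywhere else;
- a score of exactly 3 has no state;
- inactivity is undefined and can overlap both pain states, with the cut-off on a scale other than the one collected;
- a rank test is described as a comparison of means.

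The Q-TWIST therefore has no unique value under the protocol's text, whereas the AUC needs only its interval corrected. The frequency of boundary scores and the excess in the time shares rest on the assumptions shown in the working.

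The missing baseline adjustment of the AUC is an inefficiency and not an error; the gain of 9% to 25% of the variance rests entirely on the assumed correlation. Fixing the weights earlier would be good practice, but does not correct a mistake. The affected endpoints are two of the five in VI-2.

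**What to change.** In IX-1-6:

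1. Give the AUC interval as fortnightly, in line with VI-2 and VII-3.
2. Define the Q-TWIST states on the 0 to 100 scale so that each moment falls in exactly one. State what inactivity means, whether it takes precedence over the pain states or is crossed with them, and which state the boundary value belongs to. The protocol names the PASS but identifies no source for it, so the sponsor should state the assignment outright. Use one name, TWIST or Q-TWIST, throughout.
3. Describe the Mann-Whitney result as a comparison of distributions, or report a mean difference with a confidence interval.
4. Compare the AUC with adjustment for enrolment pain, and keep the Mann-Whitney test as a sensitivity analysis.

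Fixing the state weights before the blind review is worth considering while the section is open.

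The cost is protocol wording and analysis programming. The pain scores are already collected. If inactivity means being off work, the sick-leave dates in VII-3 supply it; if it means something else, the sponsor must say which collected item measures it.
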